## Abstract

**Background:** Secondary mitral regurgitation (SMR) is characterized by a pathological process impacting the left ventricle (LV) as opposed to the mitral valve (MV). In the absence of structural alterations to the MV, the expansion of the LV or impairment of the papillary muscles (PMs) may ensue. A number of technical procedures are accessible for the purpose of determining the optimal resolution for MR. Nevertheless, there is a dearth of rigorous data to facilitate a comparative analysis of MV replacement, MV repair (including subvalvular repair), and transcatheter mitral valve interventions (TMV-Is). The objective of this investigation is to evaluate and compare the efficacy and clinical outcomes of transcatheter mitral valve repair (TMV-r) utilizing the edge-to-edge mitral valve repair (TEER) procedure in comparison to conventional surgical mitral valve interventions (S-SMVis) in patients with secondary mitral regurgitation. **Methods and analysis:** A consortium of five cardiac surgery institutions from four European states and Japan have joined forces to establish a multicenter observational registry, designated TEERMISO. Patients who underwent technical procedures for SMR between January 2007 and December 2023 will be enrolled consecutively into the TEERMISO registry. The investigation team evaluated the comparative efficacy of replacement and repair techniques, utilizing both the standard surgical methodology and the transcatheter intervention. The primary clinical outcome will be the degree of left ventricular remodeling, as assessed by the left ventricular end-diastolic volume index, at 10 years. The forthcoming research will assess a variety of secondary endpoints, among which all-cause mortality will be the primary endpoint. Subsequent assessments will be made in the following order: functional status, hospitalization, neurocognition, physiological measures (echocardiographic assessment), occurrence of adverse clinical incidents, and reoperation. **Ethics and dissemination:** The multicenter design of the database is anticipated to reduce the potential for bias associated with institutional caseload and surgical experience. All participating centers possess an established mitral valve protocol that facilitates comprehensive follow-up and management of any delayed mitral complications following replacement surgery or surgical repair of the secondary mitral regurgitation. The data collected will provide insights into the impact of diverse surgical approaches on standard mitral valve surgery and TEER. This will facilitate the evaluation of LV remodeling over the course of long-term post-procedural follow-up. **Trial Registration:** ClinicalTrials.gov ID: NCT05090540; IRB ID: 202201143

What is already known on this topic? The debate over therapeutic interventions to correct secondary mitral regurgitation continues. Currently, the guidelines lack reliable long-term follow-up data. This study aims to compare the long-term clinical outcomes of patients who underwent transcatheter mitral valve procedures with those who underwent standard surgical mitral valve interventions.

What this study adds. This study will determine which of the two procedures achieves an immediate reduction in mitral regurgitation to moderate or lower levels and what percentage of patients can benefit from this result.

How this study might affect research, practice, or policy. This study will provide key information on the best treatment option between conventional mitral valve procedures and transcatheter mitral valve repair. The results can provide valuable data for the development of international guidelines.

## 1. Introduction

Secondary mitral regurgitation (SMR) is a condition that arises when the left ventricle (LV) undergoes enlargement or when the papillary muscles are compromised without any structural alterations to the mitral valve (MV). The principal characteristic of this condition is a significant alteration in the spatial arrangement of the constituent elements of the MV and subvalvular (SV) apparatus. The primary treatments for heart failure (HF) patients with SMR are guideline-directed medical therapy (GDMT), cardiac resynchronization, and coronary revascularization, which are used to optimize the treatment of the underlying LV dysfunction. The question of whether therapeutic measures aimed at improving SMR have an impact on subsequent clinical outcomes remains a topic of debate due to the fact that the disease mechanism is limited to the LV as opposed to the MV [1,2,3].

The initial and indispensable phase in the administration of all patients with SMR is the implementation of optimized pharmacological regimens in accordance with the established treatment guidelines for heart failure. This process should entail the substitution of an ACEI or ARB with sacubitril/valsartan, sodium–glucose co-transporter 2 inhibitors, and/or ivabradine if indicated [2,3].

There is no definitive evidence to support surgery for the treatment of SMR. Although restrictive mitral annuloplasty (RMA) is the most commonly used conservative technique for the standard mitral valve intervention (S-MVi), observational studies have shown that it is effective in reducing SMR and improving symptoms. However, it is uncertain whether these results are sustainable or whether the technique improves mortality compared with GDMT [4,5,6,7].

Further investigation of the long-term effects of RMA on patient outcomes is necessary to provide robust support for its use, given the conflicting results that currently exist. Patients with atrial functional mitral regurgitation typically present with a normal LVEF, less pronounced LV dilatation, and mitral annular dilatation as the primary mechanism of mitral regurgitation. This subgroup may benefit from RMA, which is frequently combined with the ablation of AF, although evidence remains limited [2]. A total of 251 patients were enrolled in the CTS Network randomized clinical trial (RCT) across 23 countries [8]. The principal objective was to ascertain the extent of reverse remodeling of the LV, as indicated by LVESV 12 months after randomization. At the two-year interim analysis, no significant intergroup difference in left ventricular reverse remodeling was observed. This was evidenced by a mean change of −6.5 mL and −9.0 mL from baseline in the chordal-sparing mitral valve repair (CS-MVRpl) and surgical mitral valve (SMV) repair (S-MVr) groups, respectively [8]. The results of the CTSN trial beyond the two-year mark will not be published due to the limitations of the study design, which did not allow for a follow-up period exceeding two years. Chordal-sparing mitral valve replacement may prove an advantageous alternative to downsizing annuloplasty repairs in patients diagnosed with coronary artery disease (CAD) and chronic severe SMR due to LV systolic dysfunction < 50% (Stage D) who require mitral valve surgery due to severe clinical symptoms (New York Heart Association [NYHA] class III or IV) that fail to remit despite optimal medical therapy for heart failure [8]. In accordance with the American College of Cardiology/American Heart Association (ACCA) guidelines, the recommendation for surgical valve replacement is classified as class of recommendation (COR) 2b and level of evidence (LOE) B-R [2,3] (Table 1).

In addition, there is a range of surgical procedures that can be employed in the treatment of mitral valve disease [9,10,11,12,13]. An RCT revealed that S-MVr was linked to comparable long-term outcomes in terms of survival rates. Nevertheless, the study also indicated an elevated likelihood of recurrent MR and cardiovascular rehospitalization in patients who underwent S-MVr in comparison to those who received chordal-sparing mitral valve replacement [8]. Nevertheless, the selection of the appropriate surgical technique remains contingent upon the experience and expertise of the surgical center and the attending surgeon [1,2,3]. In view of the paucity of clinical evidence attesting to the efficacy of two-stage MV repair, which entails a combination of subvalvular repair (SV-r) and RMA, surgeons may be disinclined to adopt this technique as a means of addressing MV issues. This conclusion is supported by observational studies [9,10] and a limited series of RCTs [11,12,13].

Two recently conducted RCTs have been completed: the Multicenter Study of Percutaneous Mitral Valve Repair MitraClip Device in Patients With Severe Secondary Mitral Regurgitation (MITRA-FR) and the Cardiovascular Outcomes Assessment of the MitraClip Percutaneous Therapy for Heart Failure Patients With Functional Mitral Regurgitation (COAPT). The efficacy of the transcatheter mitral valve (TMV) intervention (TMV-i) utilizing the MitraClip system (Abbott, IL, USA) was assessed in conjunction with GDMT and contrasted with GDMT alone [14,15,16,17]. The addition of percutaneous repair to medical therapeutic regimens did not result in a statistically significant reduction in the risk of death or heart failure readmission compared with medical treatment administered alone at the one- and two-year follow-ups in the MITRA-FR RCT [14,15]. Nevertheless, the COAPT RCT demonstrated that TEER was a safe intervention for patients with HF and moderate-to-severe or severe SMR who had not responded to GDMT. The intervention resulted in a reduced incidence of hospitalization for HF and all-cause mortality at 2 [16] and 5 years of follow-up compared to medical therapeutic regimens alone [17]. The COAPT trial represents the inaugural RCT to indicate a survival advantage resulting from the correction of secondary mitral regurgitation by means of transcatheter edge-to-edge repair. It is crucial to emphasize that the novel conceptualization of SMR pathology proposed by Grayburn et al. [18], in relation to the discrepancy in outcomes observed in the two RCTs, has prompted a renewed focus on the “MV-LV unit” and their functional interrelationships. It is of the utmost importance to contemplate these elements, as they introduce the notion of proportionate or disproportionate mitral regurgitation in the context of left ventricular size [18,19,20]. This concept serves to elucidate the prognosis of SMR, as well as to explain the differing results observed in the MITRA-FR [14,15] and COAPT [16,17] studies (Table 2).

A lack of available data precludes a direct comparison between TEER and traditional surgical techniques for the treatment of SMR. This encompasses the surgical intervention designed to address papillary muscle dislocation [7,9,10,11,12,13] and a subgroup analysis of patients who underwent CABG in comparison to those who did not [6]. Additionally, a notable proportion of patients who were enrolled in RCTs to receive TEER did not undergo PCI [14,15,16,17]. To date, only one study employed propensity score matching, which encompassed the surgical procedure of RMA [21]. In contrast, the other study did not utilize propensity score matching and centered on the edge-to-edge technique [22] and MV replacement [23].

It is hypothesized that the utilization of two distinct methodologies, based on either TEER or S-MVi, may result in disparate outcomes pertaining to survival rates, functional outcomes, and results obtained through echocardiography in the context of SMR treatment. The multicenter registry of transcatheter versus standard surgical mitral valve operation for secondary mitral regurgitation (TEERMISO) has been designed to assess the clinical outcomes of patients who received TEER using the MitraClip system in comparison to those receiving surgical mitral valve repair or replacement through a range of techniques for the treatment of secondary mitral regurgitation. This investigation presents a comparative analysis of the long-term clinical outcomes of two propensity score-matched cohorts, employing LASSO regression on a robustly sampled population cohort.

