## 3. Statistical Methods

The presentation of continuous variables will adhere to the prescribed statistical methodology, as delineated in the relevant sections of this study. The reported variables will comprise either the mean and standard deviation or the median and interquartile range, as required. With regard to dichotomous and nominal variables, the resulting data will be presented in the form of a tally and the corresponding percentage. A range of statistical tests will be employed in the univariate analysis, including the Mann–Whitney U-test, Student’s *t*-test, Kruskal–Wallis test, Wilcoxon test, Fisher exact test, Chi-square test, and Kaplan–Meier test. In the event of incomplete datasets, no attempts will be made to supplement the information in question.

Multivariable analyses will be conducted employing the logistic regression model and the Cox proportional hazards model. The variables to be included in the logistic regression analysis will be selected using the Lasso-based variable selection method. Any noteworthy inconsistencies between the study groups will be addressed through the application of propensity score weighting. To estimate the causal effect of exposure on outcomes, a doubly robust approach will be employed comprising combination regression with inverse probability treatment weighting (IPTW) by propensity score. Multivariable analyses will be conducted by employing the logistic regression model and the Cox proportional hazards model. The variables to be included in the logistic regression analysis will be selected using the Lasso-based variable selection method. Any noteworthy inconsistencies between the study groups will be addressed through the application of propensity score weighting. To estimate the causal effect of exposure on outcomes, a doubly robust approach will be employed comprising combination regression with inverse probability treatment weighting (IPTW) by propensity score. In order to accomplish this, a propensity score that balances for covariates will be developed with the objective of minimizing discrepancies between the groups in question.

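### The Introduction promises propensity-matched cohorts but Section 3 specifies IPTW, and Section 3 leaves unclear when weighting applies and which confounders Lasso may not remove

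*Protocol article*

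**What the plan says.** The last paragraph of the Introduction, which sets out the study's own aim, describes a comparison of "two propensity score-matched cohorts, employing LASSO regression on a robustly sampled population cohort".

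Section 3 (Statistical Methods) does not mention matching. It contains three statements on adjustment, each printed twice:

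- On variable selection: "The variables to be included in the logistic regression analysis will be selected using the Lasso-based variable selection method".
- On when to weight: "Any noteworthy inconsistencies between the study groups will be addressed through the application of propensity score weighting".
- On the causal effect: "a doubly robust approach will be employed comprising combination regression with inverse probability treatment weighting (IPTW) by propensity score".

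It adds that "a propensity score that balances for covariates will be developed with the objective of minimizing discrepancies between the groups in question". The covariates are not named.

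On center, the Introduction notes that "the selection of the appropriate surgical technique remains contingent upon the experience and expertise of the surgical center and the attending surgeon", and Table 4 leaves the choice between mitral surgery and TEER to each center's heart team. The Abstract states that "The multicenter design of the database is anticipated to reduce the potential for bias associated with institutional caseload and surgical experience", and Section 4.1 repeats this. The enrollment window is January 2007 to December 2023 in the Abstract and 1 January 2014 to 31 March 2023 in Section 2.

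The sample-size paragraph of Section 3 gives 630 patients (384 surgical, 246 transcatheter), 80% power and two-sided alpha 0.05.

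**The concern.** Treatment here is chosen, not randomised, so the adjustment is the main protection against confounding. The article should therefore point to one method, one set of patients and one target population.

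Matching discards patients without a counterpart and usually estimates the effect in those who can be matched. With fewer TEER patients than surgical patients, that group tends to resemble the TEER patients. Standard IPTW keeps everyone with usable data and estimates the effect in the whole cohort. The two results can differ even if both are computed correctly, and a reader cannot tell which one the study commits to.

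Two further points in Section 3 weaken the commitment. The trigger for weighting has no threshold and sits beside a sentence with no trigger at all. The only stated selection rule is Lasso, which can set a real confounder with a modest coefficient to zero. Center is a plausible confounder on the document's own account, because the center's team chooses the treatment. Procedure year is another, because the window is long. Pooling five centers does not remove center differences unless center enters the analysis.

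**Working it through.** **The two descriptions side by side**

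| Item | Introduction | Section 3 |
|---|---|---|
| Method | matched cohorts | regression plus IPTW |
| Patients analysed | only those matched | all with usable data |
| Usual target | matchable patients | whole cohort |
| When applied | always, by design | one sentence conditional on imbalance, the next unconditional |
| Role of Lasso | named beside the matched cohorts | selects for a logistic regression, not said to be the propensity or the outcome model |

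The Introduction discusses earlier matched work in a separate paragraph, so its closing sentence describes this study and not a cited one.

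**Enrollment window**

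1 January 2014 to 31 March 2023 is 9.2 years. January 2007 to December 2023 is 17.0 years.

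**Size of the difference (illustration)**

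Inputs from Section 3: 384 and 246 patients, power 80%, two-sided alpha 0.05. No effect size, SD or event rate is given, so 630 can be neither reproduced nor refuted. I solved backwards for the standardised difference d that these group sizes detect in an unadjusted comparison, by normal approximation.

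1. Full sample: d = (1.960 + 0.842) × √(1/384 + 1/246) = 2.802 × 0.0817 = 0.229 SD.
2. Matching 1:1 without replacement (ratio assumed): at most 246 pairs, or 492 patients. At least 384 − 246 = 138 surgical patients are dropped, and 138/630 = 21.9%.
3. Power with 246 pairs at d = 0.229, groups treated as independent: Φ(0.2288/√(2/246) − 1.960) = Φ(2.537 − 1.960) = Φ(0.577) = 71.8%. The detectable difference rises to 2.802 × √(2/246) = 0.253 SD.
4. Fewer pairs (assumed): 200 pairs give Φ(2.288 − 1.960) = 62.9%, and 150 pairs give Φ(1.981 − 1.960) = 50.9%.
5. IPTW with effective-sample fraction f (assumed equal in both groups): power = Φ(2.802 × √f − 1.960).

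| f | Power |
|---|---|
| 1.0 | 80.0% |
| 0.8 | 70.7% |
| 0.6 | 58.3% |
| 0.5 | 50.8% |

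6. Section 3 speaks of a rate of reverse remodeling, so I repeated the check with proportions. For assumed base rates of 20 to 50%, 630 patients detect differences of 9.9 to 11.4 percentage points with 80% power. With 246 pairs, power for the same differences is about 72%. The conclusion does not depend on the scale.

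**The case against.** The strongest reply is that one summary sentence in the Introduction is set against the operative statistical section, and that section names a single causal-effect method. This is fair. The repair is mainly a correction of wording, and the conflict does not show any intention to pick between results. It is still a conflict between two stated methods, and a later analysis plan would have to contradict one of them.

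A reader might infer several stronger points that the text does not support:

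- That weighting is used only if imbalance is seen. The sentence after the trigger states doubly robust IPTW without condition, so the text is unclear, not conditional throughout.
- That Lasso picks the propensity covariates. Section 3 ties it to a logistic regression that it does not identify, and describes the propensity score separately.
- That center and year are left out of the models. No passage excludes them, and a covariate list may properly sit in an analysis plan that is not shown. What can be criticised is a data-driven selection rule that protects nothing, together with reliance on the multicenter design.
- That standard errors will be too small. No variance method is stated.
- That IPTW preserves the planned power and matching does not. Variable weights cost power too, and over the assumed range IPTW does no better than 246 perfect pairs.

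Two supports are also weaker than they look. The Introduction's remark on center expertise concerns the choice among surgical techniques; Table 4 is the relevant text for TEER versus surgery. Section 4.2's account of changing heart failure care refers to the COAPT trial, not to this registry. The documents give no figure for the size of center or era bias.

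**Conclusion.** The point stands in this form. The article states two confounding methods that use different samples and usually have different targets. Section 3 does not settle whether weighting always applies. Its only selection rule is Lasso with no protected confounder, while treatment choice rests with each center's team over a window of 9 or 17 years. Multicenter pooling alone does not reduce center-related bias.

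The power figures are illustrations. They assume that the stated 80% refers to an unadjusted comparison, 1:1 matching without replacement analysed as independent groups, and effective-sample fractions of 0.5 to 0.8. On those assumptions matching gives at most about 72% and IPTW about 51 to 71%, so neither keeps 80%. Pairing or the outcome regression could recover some precision, and neither calculation credits this. If 630 already allows for adjustment, the loss does not arise, but the article does not say so. The change should be made; nothing here shows that the study cannot answer its question.

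**What to change.** 1. Introduction: delete the reference to matched cohorts, or label matching a sensitivity analysis.
2. Section 3: name doubly robust IPTW as the single primary analysis with the whole cohort as its stated target. Use stabilised weights, which keep that target; overlap weights would change it.
3. Section 3: replace the noteworthy-imbalance trigger with a statement that weighting applies whatever imbalance is observed. Set a balance target of standardised difference below 0.1.
4. Section 3: say which model Lasso serves. Keep center, year of procedure and key baseline prognostic variables such as baseline LVEDVI in the model, and let Lasso choose only among further candidates.
5. Before fixing item 4, check that both treatments occur at each center. Where only one does, the data cannot support a whole-cohort comparison within that center, and the plan must say how this is handled.
6. Abstract and Section 4.1: attribute control of center-related bias to the analysis, not to the multicenter design alone.
7. Sample-size paragraph: state whether 80% refers to an unadjusted or an adjusted comparison.

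The cost is wording and analysis code, using center, procedure date and routine baseline data. The downside is a few degrees of freedom and slightly wider intervals.

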## 2. Methods and Analysis

The TERMISIO prospective observational registry encompasses individuals who have been subjected to technical procedures and treatments for SMR at five cardiac surgery centers located in two European nations (France and Italy) and Japan (Table 3) over the course of nine years, from 1 January 2014 to 31 March 2023. The objective of this study is to collate data on patients who had undergone treatment during the specified period.

The goal is to obtain additional data for the purpose of future clinical research on the topic in question. The data pertaining to the successive patients with SMR will be compiled in an Access database created using Microsoft Access software, developed by Microsoft in its Redmond, Washington, USA, headquarters. The data sheet will comprise a set of predetermined variables, including those pertaining to the baseline, surgical procedure, and postoperative course of the patients. Prior to the commencement of this study, permission will be sought from the relevant institutional review board or local ethical committee in accordance with the legislation of the country in which this study is to be conducted.

